### Sample size calculation

The sample size was estimated using the G-Power software with Cohen’s *f* standardized effect size of 0.25, correlation among repeated measures of 0.25, power of 80%, and first type error of 5% based on the primary outcome measure (i.e., Utrecht Scale for Evaluation of Rehabilitation-Participation Satisfaction) [49]. The total sample size was calculated as 39 subjects which increased to 45 subjects by assuming a 15% dropout rate. In order to assure the sufficiency of the sample size, power calculation will be performed again at the end of the trial.

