## Methods

### Trial design

A parallel, three-armed, double-blinded (assessor and patients) randomized controlled trial will be conducted. Individuals will be assigned to each group in a ratio of 1:1:1 (group A: occupation-based interventions with responsibility feedback; group B: occupation-based interventions without responsibility feedback; group C: conventional interventions). The CONSORT diagram [38] will present the trial design (i.e., enrollment, allocation, and assessments) in brief (Fig. 1). This clinical trial follows the recommendations for Interventional Trials (SPIRIT) [39] statements (Additional file 1).

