### Data analysis

Data will be entered and analyzed using SPSS version 13. Each participant will have a registration number. All printed questionnaires and datasets will be stored in a secure locker and computer, respectively. Missing data will be handled by random coefficient analysis [68]. Intention-to-treat analysis will be performed for dropout participants during treatment sessions or follow-up assessments. Dropout participants will not be excluded from the sample size and data analysis. There will be no planned interim analyses and no planned stopping rules for this trial. The mean (standard deviation) or median (inter-quartile range) will be calculated for quantitative variables. For categorical variables, frequency (percentages) will be used. To check the normality of data, Shapiro-Wilk, graphical methods, and numerical indices will be used.

Quantitative demographic variables between the three groups will be compared using one-way ANOVA or Kruskal-Wallis tests. Chi-squared will be used for comparing the categorical variables between the groups. If there will be no significant difference between various outcome measures in the three groups at baseline, outcome measures will be analyzed using a 3 × 5 repeated measure analysis of variance with group (occupation-based interventions with responsibility feedback; occupation-based interventions without responsibility feedback; conventional) as between-subject factor and time (baseline, session 9, session 17, post-intervention, follow-up) as within-subject factor. A Tukey post hoc test will be performed for multiple comparisons. However, if a significant difference will be obtained for outcome measures in the three groups at baseline, a separate regression analysis will be done by considering group and baseline as covariates at each assessment point (i.e., session 9, session 17, post-intervention (week 13), follow-up (week 25)). The differences will be calculated via Kruskal-Wallis. All analyses will be considered significant with a 2-tailed *P* < 0.05.

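### The end-of-trial power recalculation cannot assure that the sample size is sufficient and, if it uses the observed effect, only restates the p-value

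*Protocol article*

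**What the plan says.** The protocol's Sample size calculation section plans the trial in advance from Cohen's f, a "standardized effect size of 0.25", a "correlation among repeated measures of 0.25", and "power of 80%, and first type error of 5" percent, all for USER-P participation satisfaction. It reports: "The total sample size was calculated as 39 subjects", then "increased to 45 subjects by assuming a 15% dropout rate". It closes with the sentence at issue: "In order to assure the sufficiency of the sample size, power calculation will be performed again at the end of the trial".

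The section does not say which effect size, variance or correlation the second calculation would use, which test it would concern, or what would follow from its result.

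The Data analysis section rules out interim analyses and stopping rules. It names a repeated-measures ANOVA with three groups and five time points, followed by Tukey comparisons, when the groups do not differ significantly at baseline. It fixes significance separately: "All analyses will be considered significant with a 2-tailed" P below 0.05. No section describes a sample-size re-estimation while recruitment is open.

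**The concern.** A calculation can assure a sample size only while the sample size can still be changed. This one is placed after the last assessment and has no decision attached, so its stated purpose cannot be met whatever inputs are used.

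There is a second difficulty if the observed effect is put into the formula. Power computed that way is determined entirely by the F statistic and its degrees of freedom. It carries the same information as the p-value in different units, yet the protocol presents it as separate evidence that the trial was large enough.

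What is at stake is interpretation. With about 15 participants per arm, the investigators may have to explain a non-significant or borderline primary result. A figure called power, planned in advance as a check of sufficiency, could then be cited to excuse the one or support the other. The uncertainty that matters is how large a group difference the data leave open, and a confidence interval shows that directly.

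**Working it through.** **Inputs.** From Sample size calculation: f = 0.25, correlation among repeated measures rho = 0.25, alpha = 0.05, target power 80%, N = 39 (45 with dropout). From Trial design: k = 3 groups ("Individuals will be assigned to each group in a ratio of 1:1:1"). From Data analysis: m = 5 time points. Assumption, because the protocol does not name the test used for sizing: the within-between interaction with sphericity (epsilon = 1).

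**Step 1. Reproduce the planned N.**
- df1 = (k - 1)(m - 1) = 2 x 4 = 8
- df2 = (N - k)(m - 1) = 36 x 4 = 144
- Noncentrality = f² x N x m / (1 - rho) = 0.0625 x 39 x 5 / 0.75 = 16.25
- Critical F(8, 144) at 5% = 2.003
- Power from the noncentral F = 0.812

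The smallest multiple of 3 that reaches 80% is 39, an exact match. With the same inputs the group main effect would need 66 and the time effect 30, so the interaction is evidently the test the trial was sized on.

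**Step 2. Power from the observed effect.** The observed noncentrality is F_obs x df1. With the degrees of freedom fixed, F_obs is the upper-p quantile of F(8, 144), so each p gives exactly one power value.

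| p | F_obs | F_obs x 8 | Power from observed effect |
|---|---|---|---|
| 0.05 | 2.003 | 16.03 | 0.806 |
| 0.10 | 1.713 | 13.71 | 0.727 |
| 0.20 | 1.403 | 11.22 | 0.621 |
| 0.50 | 0.922 | 7.38 | 0.417 |

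At N = 45 (df 8, 168) the values are 0.807, 0.729, 0.623 and 0.420, so the choice between 39 and 45 does not matter.

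**Step 3. What a pass mark of 80% would mean.** A noncentrality of 15.84 gives power of exactly 0.80 at df 8, 144. As an observed value this is F = 15.84 / 8 = 1.980, or p = 0.053. Hence reaching 80% is the same event as p of 0.053 or less.

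**Step 4. How often that mark is reached, by true power (df 8, 144).**

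| True power | Chance that observed power is at least 80% |
|---|---|
| no effect | 5.3% |
| 20% | 21% |
| 35% | 36% |
| 50% | 51% |
| 80% | 81% |

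The pass rate simply follows the chance of a significant result. A trial with 50% true power passes about half the time, and one with 80% true power fails about 19% of the time.

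**Step 5. The other reading: keep f = 0.25 and update N and rho.**
- N = 45: 0.744, 0.877 and 0.979 at rho = 0, 0.25 and 0.5
- N = 30, rho = 0.25: 0.669

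These values do not depend on the p-value. They do show how the planning assumptions turned out, but N is already fixed by then.

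**The case against.** The strongest objection is that the protocol never says the observed effect will be used. Performing the calculation again can fairly mean repeating it at the planned f = 0.25 with the achieved N and the observed correlation. Step 5 shows that this is not a function of p and says something about whether the dropout and correlation assumptions held. This stands: the equivalence with the p-value is conditional on the observed-effect reading, and a reader who infers that the protocol commits to that reading goes further than the text. What does not survive on either reading is the claim to assure sufficiency.

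A second objection is that nothing operational depends on the number. Significance has its own criterion, and no estimate, error rate or participant is affected. That also stands and limits the severity. Misuse in a later report is a risk, not something the protocol announces.

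Three further inferences are tempting and should not be drawn.
- The same p = 0.05 gives 58% for the group main effect (df 2, 42) against 81% for the interaction. This compares two different tests, and the trial was evidently not sized on the first, so the contrast is not evidence of a contradiction.
- The 81% is not universal. It assumes sphericity; at epsilon = 0.7 or 0.5, p = 0.05 maps to about 74% or 68%. The one-to-one relation remains for a given epsilon, but the near-coincidence of 80% power with significance does not.
- The point gives no ground for calling the prospective sample size wrong, since 39 reproduces exactly.

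**Conclusion.** The point holds in a limited form. A power calculation made after the trial, with no re-estimation planned and no decision attached, cannot assure that the sample size was sufficient. That conclusion needs no assumption about inputs.

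If the observed effect is used, the result is the p-value in another form. For the interaction at df 8, 144 with sphericity, the 80% mark corresponds to p = 0.053, so the check cannot tell an adequate trial from an inadequate one beyond what significance already shows.

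Severity is minor to moderate: the primary test and the prospective calculation are unaffected, and the exposure is confined to how the trial may describe its own adequacy.

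**What to change.** Delete the last sentence of Sample size calculation. In Data analysis, state that precision will be judged from 95% confidence intervals for the pairwise group differences in USER-P satisfaction (0 to 100), taken from the primary model as planned. No change of model or added baseline adjustment is needed for this. Report the achieved N, the observed SD and the observed correlation among the repeated measures, so that later trials can be sized from them. Means with SDs (or medians with inter-quartile ranges) are already planned, so the correlation is the main addition.

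If the investigators wish to keep a recalculation, the text should say that it uses the planned f = 0.25 with the achieved N and observed correlation, is descriptive only, and does not bear on the interpretation of the primary result.

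The cost is one sentence removed and one or two added, with no extra data, visits or participants.

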### Interventions

First, the importance of therapy in people with PD will be explained to participants. In each group, treatment sessions will be delivered two times a week (Sunday/Tuesday, Saturday/Wednesday, or Monday/Thursday) for 12 weeks. Each session will be approximately 60 to 90 min. Treatment sessions will be performed in the morning or evening based on the participant’s convenience and medication regime (i.e., being in “ON” state while receiving treatment). Rest will be provided for each patient as required. Participants will be instructed not to receive any other types of rehabilitation intervention during the treatment sessions. Moreover, the intervention will be discontinued when participants express their desire to terminate the intervention.

### Occupation-based interventions with responsibility feedback (group A)

This group will receive occupation-based interventions with responsibility feedbacks. These occupations and feedback statements were derived from international Delphi studies with renowned experts and national Delphi studies with people living with PD [28, 50]. Responsibility towards oneself, family members, friends, and other people in society was considered in these studies. Occupations deemed as having a very high to moderate inherent sense of responsibility based on consensus among experts and patients were chosen for designing the intervention. The derived occupations were ADL, instrumental ADL (IADL), health management, and leisure, such as maintaining personal hygiene, meal preparation and cleanup, and medication management. These occupations were approximately in common with Clarke et al.’s study [26].

The aforementioned occupations will be graded based on Gentile’s taxonomy [51]. Two general features (i.e., environmental context and function of the action) are considered in this taxonomy. Environmental context involves two characteristics with or without intertrial variability: (1) stationary regulatory conditions and (2) in-motion regulatory conditions. The regulatory conditions include surface (soft or hard/ rough or smooth/flat or inclined), space (wide or narrow), and barrier features. The function of the action encompasses body stability and body transport with or without object manipulation. Discrepancies regarding the difficulty levels of the Gentile taxonomy for each occupation were discussed and resolved in a panel of 11 experts including occupational therapists and physical therapists with at least 5 years of experience in PD rehabilitation (Table 2).

**Table 2 Tab2:** Gentile taxonomy and an example of occupation grading using this taxonomy

Environmental context	Action function				
	Body stability		Body transport		
	No object manipulation	Object manipulation	No object manipulation		Object manipulation
Stationary regulatory conditions and no intertrial variability	1A (body stability no object)	1B (body stability object)	1C (body transport no object)		1D (body transport object)
Stationary regulatory conditions and intertrial variability	2A (body stability no object)	2B (body stability object)	2C (body transport no object)		2D (body transport object)
In-motion regulatory conditions and no intertrial variability	3A (body stability no object)	3B (body stability object)	3C (body transport no object)		3D (body transport object)
In-motion regulatory conditions and no intertrial variability	4A (body stability no object)	4B (body stability object)	4C (body transport no object)		4D (body transport object)
*An example of occupation grading using Gentile taxonomy*					
Occupation	Occupation components	Difficulty components		Difficulty level	
Dressing	1-Grabbing the T-shirt 2-Folding the T-shirt 3-Raising the T-shirt for wearing 4-Putting the arms in sleeves 5-Pulling the T-shirt down 6-Grabbing the T-shirt 7-Pulling the T-shirt up 8-Taking off the T-shirt 9-Putting the T-shirt in a proper place	-Position of the individual in relation to the T-shirt or vice versa -Pace -T-shirt status or position -Environment (e.g., lighting, temperature) -Dual task (e.g., simultaneous cognitive task) -Others (e.g., shape, material, weight)		1B: sitting or standing position, pre-defined procedure within a fixed environment 2B: sitting or standing position, various performance methods within a variable environment 3B: walking, pre-defined procedure within a fixed environment 4B: walking, various performance methods within a variable environment	
*Examples of responsibility feedback statements*					
You will feel better and more satisfied with life by doing activities/occupations that you have recently gained the ability to do.					
By doing this occupation, you reduce the burden on your family members.					
You are the main interested in your improvement.					
Doing this occupation gives you a sense of empowerment.					
Doing this occupation helps you to work towards becoming independent again.					
Not doing this occupation will be disadvantageous to your family members.					

The functional level of each patient will be determined using the Gentile taxonomy. The intervention will be delivered to patients at any level of the taxonomy where they experience challenges. Participants will receive occupations from simple (i.e., stationary condition with no intertrial variability and object manipulation) to hard (i.e., in-motion conditions with intertrial variability and object manipulation) levels based on their priorities identified via Canadian Occupational Performance Measure. All patients will be actively participating in at least three to four occupations. Therefore, all participants will receive the same amount of intervention. The therapists will keep a record of the extent of participation in each occupation using a visual analog scale during each session.

Moreover, feedback statements that have the potential to create a sense of responsibility (i.e., derived from international and national Delphi studies with renowned experts and patients) in patients will be provided to participants as knowledge of performance or knowledge of the result. These feedback statements will be positive or negative statements in relation to the individual or his/her family for prevention/symptom management and function improvement. These feedback statements (i.e., based on type, target, and purpose) will be presented to the patients throughout the intervention sessions. An expert panel was held to sort the feedback statements so that patients receive all forms of feedback in each session. Some examples of responsibility feedback are provided in Table 2.

This group will receive conventional interventions (see below) for 15 min in each session. They will receive occupation-based interventions with responsibility feedback for the remaining 45 to 75 min.

### Occupation-based interventions without responsibility feedback (group B)

Participants in this group will receive occupation-based interventions (described above). Responsibility feedbacks will not be provided to this group. This group will also receive 15-min conventional interventions and 45- to 75-min occupation-based interventions.

### Conventional interventions (group C)

All the participants who are assigned to this group will only receive traditional treatment (60 to 90 min), including passive mobilization, lower extremity strengthening, stretching, motor coordination (upper and lower extremity), balance and walking training, manipulation exercises, breathing, relaxation, and postural exercises [52, 53]. Depending on the condition of each patient, they will receive these interventions. The duration and number of each therapeutic intervention will be recorded in each session.

### Measurements

Demographic and PD-related information including age, gender, education, family status, marital status, job status, assistive device use, fall history, years since diagnosis, and medications will be collected from participants. Outcome measures will be assessed by a blind certified occupational therapist at baseline, session 9, session 17, post-intervention, and follow-up.

### Primary outcome measure

The primary outcome of this trial will be participation satisfaction assessed with the Utrecht Scale for Evaluation of Rehabilitation-Participation Satisfaction Scale (USER-P). The satisfaction scale consists of 10 items including vocational activities, leisure activities, and social relationships. Each item will be rated on a 5-point Likert scale. The summation of scores will be converted to a 0–100 scale, with higher scores indicating greater participation satisfaction [54]. The Persian version of the USER scale has shown appropriate validity and reliability [55].

### Secondary outcome measures

Secondary outcomes will include participation frequency and restriction, motivation, and volition as well as sense of agency, responsibility, physical activity, community integration, ADL and IADL, upper extremity function, balance, fatigue, and quality of life.

Several psychometric scales will be employed for these secondary outcome measures, as follows:

Participation frequency and restriction

*Frequency and restriction scales of USER-P* will be regarded for measuring this outcome. The frequency scale consists of two parts. Part A measures the time (0 = not at all; 5 = 36 h or more) spent on paid work, unpaid work, volunteer work, and housekeeping. Part B measures the frequency (0 = not at all; 5 = 19 times or more) of social and leisure activities. The restriction scale evaluates restrictions experienced while participating in daily activities. Items will be scored as not applicable (NA), not possible (1), with assistance (2), with difficulty (3), and without difficulty (4). The sum scores in these two scales will be converted into a 0–100 scale (54).

Self-perceived performance and performance satisfaction

*Canadian Occupational Performance Measure* will be used to evaluate the self-perceived occupational performance and satisfaction with a semi-structured interview in areas of self-care, productivity, and leisure [56].

Motivation

*Social Motivation Questionnaire* will be used to measure the information-seeking (4 items) and emotion-regulatory behavior (4 items) motivation for social participation. Each item will be graded between 1 (very disagree) and 7 (very agree). Higher scores will denote stronger information-seeking and emotion-regulatory behavior motivation [57].

Volition

*Volitional Questionnaire* is a MOHO tool which will evaluate volitional development via observing individuals while performing occupations with 14 items. Items will be rated as follows: 1 = passive, 2 = hesitant, 3 = involved, and 4 = spontaneous. Higher scores will represent a higher level of volition [58].

Sense of agency

*Intentional Binding Task* measures the implicit sense of agency. Subjects will be asked to judge the time of actions (i.e., key press) and effects (i.e., tones) via a clock hand rotating around a clock face on a computer screen. This task contains two baseline (tone, action) and two operant (tone, action) conditions [59].

Responsibility

*Allocation of Treatment Responsibility Scale* will evaluate the responsibility during medication-related tasks for caregivers and patients with two parallel forms. Each item is rated from 1 (none of the time) to 4 (all the time). The total score will be the summation of items, with higher scores reflecting increased perceived responsibility [60].

Physical activity

*Phone Frequency, Intensity, Time, and Type (Phone-FITT) Questionnaire* will measure the physical activity participation in household (6 items) and recreational (11 items) activities. The frequency and duration of each activity will be asked. The duration is rated on a 4-point scale (0 = 0 min; 1 = 1–15 min; 2 = 16–30 min; 3 = 31–60 min; 4 = 1 h and more). Higher scores will indicate greater levels of physical activity participation [61].

Community integration

*Community Integration Questionnaire-Revised* will evaluate the individual’s integration into home and community with 18 items. Most items will be rated on a scale of 0 to 2, with 2 representing greater integration. Subscale scores will be calculated as follows: home integration (0–12), social integration (0–10), productivity (0–7), and electronic social networking (0–6). Higher scores will reflect a higher degree of community integration [62].

ADL and IADL

*Nottingham Extended ADL Scale* will be used to assess the level of independence in mobility, kitchen, domestic, and leisure activities. Each item will be scored with 4 (no (0 points), with help (1 point), on my own with difficulty (2 points), and on my own (3 points)) response options. A higher total score will indicate greater independence [63].

Upper extremity function

*9-Hole Peg Test* will be used to evaluate hand dexterity. The participant will be asked to pick pegs one by one from the container and place them into the holes on the board as quickly as possible. Participants must then remove the pegs one by one and replace them back into the container. The time taken to complete this procedure will be recorded for each hand [64].

Balance

*Dynamic Gait Index* will evaluate the patient’s ability to maintain balance while walking with different task demands in 8 dynamic conditions. Items will be rated on a 4-point Likert scale. The total score will range between 0 and 24 points, with higher scores denoting better performance [65].

Fatigue

*Fatigue Severity Scale* will be used to measure the effect of fatigue on daily functioning. This scale consists of 9 items, rated from 1 (completely disagree) to 7 (completely agree). Higher scores will indicate severe fatigue [66].

Quality of life

The *Parkinson’s Disease Questionnaire (PDQ-39)* will be used to evaluate health-related quality of life across dimensions of daily living. Items will be rated on a 5-point Likert scale (0 = never; 4 = always). Each domain’s score will be calculated by the sum of scores of items in the domain divided by the maximum possible score of the domain, multiplied by 100 [67].

